# Ocular Rosacea microBiome Study (ORBS)—sub-microbial versus antibiotic dosing of doxycycline versus placebo in treatment of symptomatic ocular rosacea: study protocol for a parallel-arm randomized clinical trial

**DOI:** 10.1186/s13063-022-06948-9

**Published:** 2022-12-20

**Keywords:** Ocular rosacea, Microbiome, Doxycycline, Sub-microbial, Antimicrobial resistance

## Abstract

**Background:**

Ocular rosacea is common and is often managed with long-term antibiotic treatment. Doxycycline is the most commonly selected antibiotic for the treatment of rosacea. As there is no established standard of care treatment dose for rosacea, prescribed doses of doxycycline vary widely. The FDA classifies 40 mg daily dose of doxycycline for ocular rosacea as sub-microbial in comparison to an antibiotic dose of 200 mg daily. However, this “sub-microbial” dose has never been evaluated in patients with ocular rosacea, and even the sub-microbial dose has potential to alter systemic mucosa flora. Here, we present a randomized controlled trial using RNA sequencing to fully characterize the impact of sub-microbial antibiotic dosing of doxycycline on antimicrobial resistance and bacterial composition of the ocular and gut flora.

**Methods:**

In a triple-masked parallel randomized control trial, patients with ocular rosacea will be randomized to three arms: a 40-mg dose of doxycycline, a 200-mg antibiotic dose of doxycycline, or placebo. Collected rectal and lower eyelid samples will be compared for frequency of antimicrobial resistance genetic determinants and microbiome diversity. A subjective ocular surface disease index survey and objective tear breakup time measurement will be determined.

**Discussion:**

These results will enhance our understanding of the overall systemic impact of long-term systemic sub-microbial antibiotic dosing for the treatment of chronic recurrent ocular inflammatory diseases.

**Trial registration:**

This trial was registered on ClinicalTrials.org (NCT05296837) on March 22, 2022.

**Supplementary Information:**

The online version contains supplementary material available at 10.1186/s13063-022-06948-9.

## Introduction

Ocular rosacea is an inflammatory disease of the eyelids and ocular surface [1]. Like the facial disease, the ocular condition is chronic and recurrent. Sequelae of ocular rosacea vary from mild to severe. Ocular rosacea may cause chronic eye redness, blepharitis, recurrent chalazion dry eye, corneal erosion, corneal vascularization, and corneal ulceration (Fig. 1). Resulting corneal opacity can result in vision loss [2].

**Fig. 1 Fig1:**
[figure not shown]
Clinical examples of ocular rosacea. **a** Eyelid margin findings in a patient with ocular rosacea: upper (i) and lower (ii) eyelids with lid margin telangiectasia and Meibomian gland clogging. **b** Corneal neovascularization and peripheral keratitis in a patient with ocular rosacea

Topical antibiotic and anti-inflammatory eye drops and ointments can be used to control mild ocular rosacea. However, severe disease, or rosacea that is not well controlled with local treatments, is treated systemically [3]. The most commonly used systemic treatment for rosacea is the bacteriostatic antibiotic doxycycline [3, 4]. Rosacea treatment regimens of doxycycline vary widely [5]. Treatment-dose doxycycline for systemic infections is 200 mg a day. However, as rosacea is considered an inflammatory disease, doxycycline is often dosed at what is termed, sub-microbial dose doxycycline (SDD). Initially introduced in the oral medicine literature, SDD are doses 40 mg and lower because systemic administration at this dose does not appear to alter the oral mucosa flora or increase resistance rates when given long-term for periodontal disease [6, 7]. Whereas 200 mg doxycycline, even when given short term, may increase the percentage of culturable nasopharyngeal flora that is resistant to doxycyline [7, 8]. The FDA does not categorize SDD an antibiotic, stating this dosing is expected to exhibit only anti-inflammatory activity [6].

SDD is widely used for the treatment of rosacea, and though previous studies have shown a 40 mg dose does not affect oral flora microbiome and resistance, further research on other systemic mucosa’s flora is needed [6]. Data provided by the manufacturer showed that administration of 20 mg doxycycline twice daily to healthy adults resulted in concentrations of antimicrobial-resistant bacteria below the minimum antimicrobial level at 24 h after administration [8].The classification of 40 mg as “sub-microbial” has never been evaluated in patients diagnosed with ocular rosacea. Additionally, confirmation of a “sub-microbial” dose has not been investigated with more sophisticated recently available genomics and resistance tools such as unbiased RNA deep sequencing (RNA-seq).

The goal of this proposal is to use RNA-seq to determine whether SDD given to patients with ocular rosacea can be truly considered sub-microbial, or if a 40 mg dose of doxycycline can in fact alter the microbiome of the ocular surface and gut and increase resistance rates when prescribed for up to 8 weeks. We plan to evaluate the effect of SDD on antimicrobial resistance and microbiome alteration through a randomized controlled masked trial.

The objectives of this trial are to investigate if there are detectable alterations in tetracycline antimicrobial resistance gene expression and microbiome of the ocular surface and gut with administration of SDD for the treatment of ocular rosacea. Our specific aims are to investigate (1) alterations of antimicrobial resistance (AMR) in the gut and ocular surface, (2) alterations to the gut and ocular surface microbiota, and (3) changes in conjunctiva immune response expression. We hypothesize equivalency in that doxycycline at both the antibiotic treatment dose (200 mg) and SDD dose (40 mg) will increase tetracycline resistance gene expression, alter microbiota, and alter immune response genes relative to placebo.

## Methods

### Study design

The Ocular Rosacea microBiome Study (ORBS) is a three-armed, parallel, randomized, masked, placebo-controlled clinical trial. Participants with a diagnosis of symptomatic ocular rosacea (*n* = 50) at the University of California, San Francisco in San Francisco, California, United States, will be prospectively enrolled and randomized to one of three arms in a 2:2:1 fashion. (1) Arm A, a SDD dose of doxycycline (40 mg) taken for 8 weeks; (2) Arm B, an antibiotic dose of doxycycline (200 mg) taken for 8 weeks; and (3) Arm C, a placebo pill taken for 8 weeks. The trial will begin enrollment in December 2022. This protocol adheres to the Standard Protocol Items: Recommendations for Interventional Trials (SPIRIT) guidelines (Supplementary Table S1) and is registered on clinicaltrials.org (NCT05296837) [9]. This study was reviewed and approved by the Institutional Review Board at the University of California, San Francisco (21–34725) and will be done in accordance with the Declaration of Helsinki.

### Setting, participants, and eligibility

The study setting for this trial is the ophthalmology clinics at the F.I. Proctor Foundation and Department of Ophthalmology and the dermatology clinics at the University of California, San Francisco (UCSF). Participant recruitment will include treating clinicians referring patients with ocular rosacea to one of the study staff listed on the protocol. The study coordinator will review the patient’s clinical information to determine if they are eligible for the study. The study staff members will approach, and consent interested participants for the study.

Inclusion criteria for this study include if the participant has (1) symptomatic ocular disease attributed to ocular rosacea as the primary diagnosis, (2) the ability the give informed consent, and (3) is age 18 years old or older as doxycycline is contraindicated in children under 10 years old. Patients with ocular rosacea will be excluded from study participation if they have (1) an active ocular or systemic infection, (2) a known allergy or intolerance to tetracycline antibiotics, (3) prior use of oral antibiotics within the last three months, or (4) pregnancy or the possibility of becoming pregnant within the 8-week study medication timeline as tetracyclines are considered teratogenic.

### Intervention and sample size

The study coordinator will offer a sealed container to each participant during their primary visit. Each day’s dose will be marked in individual AM/PM packets. The coordinator will instruct the patients to take both doses, AM and PM, daily for 8 weeks. Participants taking 40 mg doxycycline will be taking one 20 mg doxycycline pill twice a day. Participants taking 200 mg doxycycline will be taking 100 mg twice a day. Participants allocated to placebo will be taking a placebo pill twice daily. The initial dose will not be offered under clinical observation as the pills for each study arm will look different and can unmask the participant to the study team. Participants will bring medication to all follow-up visits, compliance will be monitored by pill count performed by the study monitor. Monitoring for systemic side effects will be done at study follow-up visits via a questionnaire. We will not take objective measurements of adherence such as blood levels due to inefficiency and cost in this modest sample cohort.

We estimate that twenty patients per arm will provide over 80% power to detect a twofold increase in tetracycline resistance genetic determinants between Arms A and B, assuming the standard deviation in read number found previously, allowing for 10% dropout, and correcting for baseline [10]. As a secondary analysis, we estimate that twenty patients in Arm A and ten in Arm C will provide over 80% power to detect a three-fold increase in tetracycline resistance genetic determinants.

We estimate that twenty patients per arm will provide over 80% power to detect a difference between Arms A and B in Shannon’s diversity effective number of 2 (from an effective number of 10. That is, 10 to 8 or 10 to 12 effective number), assuming 10% drop-out and a standard deviation in the effective number of 1.9, found in two previous studies [11, 12]. As a sensitivity analysis, we anticipate similar power using Simpson’s diversity (again, expressed as an effective number).

### Randomization and masking

The study statistician will create a permuted block allocation sequence in R Foundation for Statistical Computing, to prevent overt imbalance in this modest-sized trial. The clinical study coordinator will then perform study randomization according to the 2:2:1 randomization schedule using the REDCap (Research Electronic Data capture) tool randomization module to allocate patients to groups. All study arm medications will be centrally located in sealed containers that the study coordinator will hand out according to randomized allocation. We will use letters, A, B, and C, to mask treatment arms. All patients will be masked to their SDD allocation and informed that they will be taking a pill by mouth twice a day. All examining physicians responsible for tear breakup time (TBUT) determination and ocular photography will be masked to patient allocation assignment. One biostatistician will generate the randomization key and another will perform outcome analysis masked to patient allocation assignment. Only the study coordinator, one biostatistician, and one study coordinator from a separate project will have access to the randomization key. Emergency unblinding is acceptable if a participant experiences an adverse event.

Doxycycline at 40 mg and 200 mg and placebo will be purchased from the vendor, Amerisource Bergen.

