### Study oversight

A Data and Safety Monitoring Committee (DMSC) created before the study begins will provide independent oversight of data quality and participant safety at annual committee meetings. The committee will review the number of patients and any significant adverse events. If necessary, the study analyst will provide unmasked treatment assignment to the committee. The DSMC will recommend modifications to the study protocol as necessary. Major protocol changes will be reported to the DSMC and Institutional Review Board (IRB) as required. Important protocol amendments will be communicated to all parties including the study team and trial participants via secure email.

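### The masking letters A, B and C are the published arm names, so they do not mask a protocol reader who sees them, and one code is shared by a whole arm

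*Protocol article*

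**What the plan says.** Study design names the arms by letter. The first is "Arm A, a SDD dose of doxycycline (40 mg) taken for 8 weeks", the second is "Arm B, an antibiotic dose of doxycycline (200 mg) taken for 8 weeks", and arm C is placebo. It gives 50 participants allocated 2:2:1. The sample-size text uses all three letters in its power statements, and Statistical considerations uses A and B.

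Randomization and masking then gives the masking device: "We will use letters, A, B, and C, to mask treatment arms". The same section has one biostatistician generate the key, while "another will perform outcome analysis masked to patient allocation assignment". It limits access to the key to three roles: the study coordinator, one biostatistician and a coordinator from another project. It also says "Emergency unblinding is acceptable if a participant experiences an adverse event". The abstract calls the trial triple-masked.

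Three other statements bear on the point:
- The section on intervention and sample size admits that "the pills for each study arm will look different and can unmask the participant to the study team".
- Study oversight says that, if necessary, "the study analyst will provide unmasked treatment assignment to the committee".
- The section on outcomes assessment describes arm B as placebo in defining the primary comparison, which contradicts Study design.

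**The concern.** A masking code works only if its key is hidden from the people it is meant to mask. Here the key is printed in the article. The outcome biostatistician cannot avoid reading it, because the same document defines the comparisons to be run.

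The primary outcome is a resistance-gene load derived from sequencing. Data processing, exclusions and model details can be settled after the data exist, and a masked analyst is one of the plan's stated safeguards over those choices. OSDI is self-reported, and TBUT may be timed by a physician where no automatic device is available. Both therefore also rely on masking, although both are exploratory.

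A second weakness would remain even if the letters were secret. A code shared by an arm lets knowledge of one participant spread to others.

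**Working it through.** **Inputs.** N = 50 and ratio 2:2:1 (Study design); twenty per arm in A and B and ten in C (Intervention and sample size); one letter per arm (Randomization and masking).

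**1. Arm sizes.** 50 × 2/5 = 20, 50 × 2/5 = 20, 50 × 1/5 = 10. This reproduces the article's twenty, twenty and ten.

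**2. The two sections side by side.** Study design assigns A, B and C to 40 mg, 200 mg and placebo. Randomization and masking uses A, B and C as the mask. The article describes no second, scrambled set of letters and no participant-level code.

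**3. How many letter-to-arm keys remain possible.** Three letters can be matched to three arms in 3! = 6 ways. If the group sizes are seen, the group of 10 must be placebo, which leaves 2! = 2. One unblinding in an active arm then leaves 1. If sizes are not seen, one unblinding fixes one letter and leaves 2.

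| Code in use | Keys possible | After sizes are seen | After one unblinding in an active arm |
|---|---|---|---|
| Letters as published | 1 | 1 | 1 |
| Three unrelated letters, sizes seen | 6 | 2 | 1 |
| Three unrelated letters, sizes not seen | 6 | not applicable | 2 |

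With the letters as published there is nothing left to discover. With three unrelated letters the mask is partial: placebo shows by its size, but 40 mg and 200 mg stay hidden from each other until an active-arm participant is unblinded.

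**4. Spread from one unblinding.** With a shared arm code, the others exposed are 20 − 1 = 19 in either active arm, or 10 − 1 = 9 in placebo. These are upper limits: they apply only to someone who also sees those participants' letters. With a unique number per participant, the number of others exposed is 0.

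**5. How likely is at least one unblinding?** The article gives no rate, so these per-participant rates p are assumptions, with participants taken as independent. The formula is 1 − (1 − p)^50.

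| Assumed p | Chance of at least one among 50 |
|---|---|
| 1% | 39.5% |
| 2% | 63.6% |
| 5% | 92.3% |
| 10% | 99.5% |

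Even a low rate makes one event during the trial plausible. None of this enters the sample size, power or alpha.

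**The case against.** The strongest reply is that a journal article condenses a fuller protocol, and that the coding of a masked file is commonly left to that document or to the analysis plan. The article says the outcome analyst is masked and restricts the key to three roles. That answers a stronger reading which a reader might infer: that the analyst is certainly unmasked and all 50 assignments are readable. No section says which codes the analysis file carries, so that reading is an inference. What survives is that the article does state its masking method, and the method as stated cannot do its job. That is a rule fixed badly, not a missing detail.

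Further points for the plan:
- **Who sees the letters.** Containers are sealed, lid-swab tubes carry a patient ID sticker, samples are de-identified and examining physicians are masked. No section says that letters are printed on containers. This limits how far an unblinding spreads, and the limit stands.
- **Unblinding.** A reader might take the rule to allow unblinding for any adverse event. The sentence begins with the word emergency, so that is too broad, although it adds no severity threshold. The article does not say who would learn the result.
- **Visible pill differences.** A reader might infer that returned medication unmasks the assessors. The article avoids an observed first dose and gives pill counts to the study monitor, not to the examining physicians. This is largely answered.
- **Assignments to the committee.** The study analyst can be read as the biostatistician who holds the key. The wording is ambiguous and does not show a breach.
- **Group size.** That a smaller arm reveals itself is inherent in 2:2:1 allocation analysed by group. It is not an error of this plan.
- **Other safeguards.** Reproducible processing scripts are planned and automatic TBUT is preferred, so masking is not the only protection.

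The conflicting label for arm B does not rescue the mask. An inconsistency is not a concealment scheme.

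**Conclusion.** The point holds in this form. The stated masking code is the published arm name, so it hides nothing from a protocol reader who sees a letter. Whether that includes the outcome biostatistician depends on whether the analysis file carries the letter. If it does, the masking claimed in the abstract and in Randomization and masking fails for that person.

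The shared code also means that one emergency unblinding can reveal up to 19 others, or 9 in placebo, on the condition that whoever learns it can see their letters. The documents do not allow any resulting bias to be sized; the figures count exposed assignments only. The change should be made because a stated safeguard does not work as written and repair is cheap.

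**What to change.** In Randomization and masking, replace the sentence on letters with wording to this effect: containers carry numbers unique to each participant; the masked analysis file uses neutral codes unrelated to the published arm names; the key-holding biostatistician holds the map; and the map is released only after data and analysis code are locked.

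In Study oversight, say that this key-holder, and not the masked outcome analyst, supplies assignments to the committee.

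Reconcile the label of arm B in the outcomes section with Study design.

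Optional: split each active arm into two codes, so that there are 2 + 2 + 1 = 5 codes of about 10 participants and size no longer points to placebo. The downside is that the planned three-arm ANOVA and the A-versus-B comparison can be run only once codes are merged. The main fix does not depend on it.

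The cost is revised wording and relabelling at packing, with no added participants.

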The study coordinator will obtain patient consent before collection. A sample collection tube labeled with the patient’s ID sticker will be filled with 1 ml of Zymo solution to stabilize the RNA/DNA in the sample. The collection kit will also contain an applicator swab, tube rack, and parafilm to prevent leakage after collection.

For sample collection, the physician will wear gloves and a mask, and instruct the patient that neither of them should speak during swabbing as RNA-seq is very sensitive and can pick up oral flora contamination in the air. No anesthetic drops will be used to further limit contamination. The physician will swab the first eye using the polyester tipped applicator swab (Fig. 2a), pulling down the lower eyelid and rolling the swab across the length of the inferior lid margin twice, while rotating the swab, and then repeating in the second eye. The order of eyes swabbed is inconsequential as both eyes will be swabbed with the same applicator. The physician will then open the sterile capped plastic tube container, place the swab tip down, and carefully snap the swab while holding the tube steady with the other (Fig. 2b). Immediately after capping the plastic tube, they will stretch the parafilm over the top for further leak protection (Fig. 2c) before placing the tube back on the rack.2)Rectal swab collection

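### Allocation concealment is not secured as written: the study coordinator who reviews eligibility and performs randomization also has access to the randomization key

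*Protocol article*

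**What the plan says.** Four tasks fall to the study coordinator in the protocol article.

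- **Eligibility** (Setting, participants, and eligibility): "The study coordinator will review the patient’s clinical information to determine if they are eligible for the study".
- **Randomization** (Randomization and masking): "The clinical study coordinator will then perform study randomization according to the 2:2:1 randomization schedule using the REDCap (Research Electronic Data capture) tool", within that tool's randomization module.
- **Dispensing** (Intervention and sample size): "The study coordinator will offer a sealed container to each participant during their primary visit". Randomization and masking repeats that the coordinator hands out the containers.
- **Key access** (Randomization and masking): "Only the study coordinator, one biostatistician, and one study coordinator from a separate project will have access to the randomization key".

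The sequence is a permuted-block list made by a statistician in R, in a 2:2:1 ratio, with no block size given. Each arm has one fixed letter: A, B or C. Patients, examining physicians and the analysing biostatistician are masked.

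The consent tasks are divided. Setting, participants, and eligibility says: "The study staff members will approach, and consent interested participants for the study". The lid-swab procedure says: "The study coordinator will obtain patient consent before collection".

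**The concern.** Concealment requires that whoever decides whether and when a patient enters cannot know or predict the next assignment. Here the role that reviews eligibility is also a key-holder. The list of holders separately names a coordinator from another project, so the first-named coordinator is most naturally this trial's own.

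Eligibility leaves room for judgement, because symptomatic eye disease must be attributed to rosacea as the primary diagnosis. The exclusion for oral antibiotics reaches back only three months, so patients with older tetracycline exposure can enter. Such exposure could plausibly bear on the primary outcome, the load of resistance determinants. With 50 participants split 2:2:1 (20, 20 and 10), a few entries hastened, delayed or declined with the next arm in mind could shift an arm's make-up. Baseline correction adjusts for measured baseline values, not for unmeasured differences that selection may bring.

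**Working it through.** The plan states no figure on this point to reproduce. The check has two parts.

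**1. Do the stated safeguards separate the eligibility decision from the key?**

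| Safeguard in the article | What it protects | Does it close the gap? |
|---|---|---|
| REDCap randomization module | Hides the next assignment from users without the list | Not for someone who holds the list |
| Sealed containers, arm letters | Hide treatment from those without the code | Not for a key-holder |
| Masked examining physicians | Tear break-up time and photography | No, acts after entry |
| Masked analysing biostatistician | Outcome analysis | No, acts after entry |

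No section says that the coordinator's access begins only after enrolment or covers only past assignments.

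**2. How predictable are assignments under each meaning of the key?** The article does not define the term.

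*Broad reading: the key is the allocation list.* Its holder can look up every upcoming assignment.

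*Narrow reading: the key only decodes the letters.* The coordinator still sees each letter released and knows what it means. Inputs are the 2:2:1 ratio, permuted blocks and fixed letters (all from the article), plus an assumed block size that the coordinator knows. With a, b and c assignments left in the block and T = a + b + c, the best guess is correct with probability max(a, b, c)/T. The expected number of correct guesses is

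g(a,b,c) = max(a,b,c)/T + (a/T)·g(a−1,b,c) + (b/T)·g(a,b−1,c) + (c/T)·g(a,b,c−1), with g(0,0,0) = 0.

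By hand for a block of 5 (AABBC):

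- Position 1: 2/5 = 0.400.
- Position 2: 2/4 = 0.500, whichever arm came first.
- Position 3: the first two are one A and one B with probability 0.4, leaving one of each arm (best guess 1/3). Otherwise the best guess is 2/3. So 0.4 × 1/3 + 0.6 × 2/3 = 0.533.
- Position 4: the last two match with probability 0.2 (certain), otherwise 1/2. So 0.2 × 1 + 0.8 × 0.5 = 0.600.
- Position 5: 1.000.

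Mean: (0.400 + 0.500 + 0.533 + 0.600 + 1.000)/5 = 0.607.

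Share known with certainty, block of 5: position 5 always (1/5 = 0.20), plus position 4 when the last two match (0.2 × 1/5 = 0.04). Total 0.24.

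| Assumed block size | Correct best guesses | Always guessing one larger arm |
|---|---|---|
| 5 | 0.607 | 0.40 |
| 10 | 0.559 | 0.40 |
| 15 | 0.534 | 0.40 |

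Over 50 participants, a block of 5 gives 0.607 × 50 ≈ 30 correct guesses against 0.40 × 50 = 20. A block of 10 gives 0.559 × 50 ≈ 28. A block of 15 does not divide 50, so its figure applies to complete blocks. Five is the smallest block that gives 2:2:1, so 61% and 24% are the worst case.

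**The case against.** The strongest reply is that the article never defines the key. It speaks of a sequence, a schedule and a key, and nowhere says that the coordinator sees upcoming assignments. It also describes a statistician-made sequence, release through REDCap and sealed containers. This stands, and it rules out some stronger readings.

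- **That concealment is absent and every assignment is foreknown.** A reader might infer this, but it holds only if the key is the forward list. That reading is plausible, partly because the Study design section already ties each letter to a treatment, but it remains an inference.
- **That the coordinator enrols participants.** The article gives approach and trial consent to study staff. The coordinator's stated consent task is placed in the swab procedure. The article also uses the plural, coordinators, once, so it is inferred that one individual does everything. The concern needs only the eligibility review, which is assigned explicitly.
- **That the triple-masked description fails.** Patients, examining physicians and the analyst are three masked parties, a natural meaning of the term. No section claims that the coordinator is masked.

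It is also fair that a sequencing outcome corrected for baseline and a masked analyst limit the damage, that the three-month antibiotic exclusion narrows the exposure example, and that no bias in the primary outcome has been quantified. The percentages measure predictability only. None of this separates the eligibility decision from the key. Nor is it a gap left by condensing the full protocol, because the article states the arrangement outright.

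**Conclusion.** The concern holds as a weakness in the procedure as stated: allocation is not secured against the role that judges eligibility. Its size depends on what the key is. Upcoming assignments are fully knowable if it is the list. If it is only the letter code, about 53% to 61% can be guessed against 40%, assuming blocks of 5 to 15 and a coordinator who knows the block size. What is shown is an opportunity for selection bias, not that bias will occur.

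That the roles overlap is explicit in the text. How much can be foreseen is less certain, because the key is undefined. The change should be made before the first randomization, since concealment cannot be restored for participants already allocated.

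**What to change.** Amend Randomization and masking, and align the dispensing text in Intervention and sample size, as follows.

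1. Remove this trial's study coordinator from the key-holders. The randomizing biostatistician and the already-named coordinator from a separate project remain, and they become the contacts for the emergency unblinding that the section allows.
2. At dispensing, replace the arm letters with uniquely numbered sealed containers prepared by the separate-project coordinator.
3. Set REDCap user rights so that it releases only the container number, and only after eligibility and consent are locked.

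The cost is container preparation, a change of user rights, and edits to the text on key access, letters and dispensing. No new post is needed. One limit remains: the article says that the pills look different by arm and are brought to follow-up visits, so site staff may still learn some past allocations. The change closes direct access to the key and the run of visible letters, but it does not make the coordinator fully masked.
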